## 7.6 Study procedures

After screening (medical history, physical examination including blood pressure, laboratory check, ECG, questionnaire [general health, disease history, physical activity, lifestyle]), and approval of the cardiologist, patients will be included in the study. Patients will undergo several tests at one testing day. Testing will be performed at T0, T1 and T2 (figure 2).

[figure not shown]

Figure 2. Study procedures

**Testing day: Blood samples, Physical Fitness and Questionnaires (2 hours) (See Appendix I-Schedule of events)****Blood samples**

Blood samples will be obtained for the analyses of a number of CVD risk parameters (e.g. HDL, LDL, HbA1C) and renal function.

**Physical fitness**

Before the assessment of physical fitness, skinfold thickness will be determined (biceps, triceps, sub-scapular, supra-iliac) to calculate the lean body mass. (13)

Physical fitness level will be measured as the  $VO_{2peak}$  during an incremental maximal exercise test, using a continuous gas analyser. ECG and heart rate will be registered continuously and blood pressure will be measured at fixed intervals of 3 minutes. The test will be performed under supervision. The modality for the exercise test will be cycling. All tests will be performed by the same protocol. For patients who are not able to participate in a  $VO_{2peak}$  test, this test will be replaced by a 6 Minutes Walking Test. The testing modality chosen per centre at T0, will remain the same at T1 and T2. To ensure a safe environment in which the tests can be performed, the test will be performed to applicable guidelines and regulations within each participating centre.

**Questionnaires**

After the incremental maximal ergometer exercise test, subjects will be asked to fill out four validated questionnaires to assess general health. This includes quality of life (SF-36v2), level of anxiety (GAD-7), level of depression (PHQ-9) and dietary pattern (Mediterranean Diet Score) of the patient. (14-20) These postal questionnaires will be completed at T0, T1 and T2. All questionnaires are easily completed within 30 minutes.

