## 6. TREATMENT OF SUBJECTS

### 6.1 Investigational product/treatment

Patients participating in the *mCR* programme (or intervention group) will undergo 6 months of mobile telemonitoring guidance and in addition another 6 months without mobile telemonitoring. The *mCR* group receives a heart rate monitor and smartphone with a special application to use for their training in their home environment. This smartphone can only be used by the patient for research purposes and will be given back to the researcher once the patient finishes the first 6 months in the study with mobile telemonitoring guidance. Instructions are given to the patient by the researcher, nurse or physician before they start training with a heart rate monitor and smartphone at home. Patients are instructed to exercise while wearing the heart rate monitor at 5 days per week for at least half an hour at an individual selected level of intensity and self-chosen type of activity. The outcomes of the maximal exercise tests on the first visit will enable to personalise the heart rate zones per patient in order to see (after every training/activity) in what zone the patient is training. At the moment patients start an exercise, they need to wear the heart rate monitor, and select on their smartphone the type of activity they are going to perform. While finishing the exercise patients have to register at the smartphone they are done and fill in the rate of perceived exertion (BORG-score). Accordingly, the duration, intensity (based on the heart rate zones) and BORG-score of each training/activity is collected by the smartphone and transferred to a secured website where both patient and researchers/nurses involved in the study can view the results. During the first month patients receive weekly individual coaching and feedback on their training results by telephone, in the second month this will be once per two weeks, whereas one monthly call will be held in the last four months (month 3 until 6) of the mobile telemonitoring period. Mobile telemonitoring guidance will help to improve the self-management skills and stimulate a patient to exercise independently. Besides the coaching by telephone and the advice to train 5 days a week for a minimum of 30 minutes at the start of the first 6 months, there will be no other advices given by the researcher, nurse or physician via the smartphone or secured website. At the end of the first 6 months, the patients are asked to return the heart rate monitor and smartphone to the researcher. In the second period without mobile telemonitoring (month 7 until 12) patients will receive no coaching or feedback by phone. Cardiac patients that are randomised to the control group will undergo 6 months with no *mCR* programme with another 6 months of follow-up in addition. During the study period both groups will receive standard outpatient care and control by a cardiologist. See paragraph 6.2 for more information about the way data are collected by the smartphone in the intervention group.

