### 7.5 Randomisation, blinding and treatment allocation

At the start of the CR programme, once patients have indicated not to be interested in the regular CR programme, patients will be informed about the study and requested to participate. After receiving written consent from the patient they will be randomised in 1:1 ratio to the intervention group with mobile telemonitoring guidance or the control group with no mobile telemonitoring guidance or other CR programme by means of computerised allocation system applying an algorithm that prevents the care providers or the investigators from predicting the outcome of the randomisation

process. This means that the person, who determines if the patient is eligible, at the time of this decision, is unaware of which group the patient will be allocated to. The patient, care provider and outcome assessor will not be blinded to the intervention itself because of safety concerns.

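### Self-report questionnaires are placed after the maximal exercise test and called postal, although they belong to the testing day; one mode, and completion before the test, should be fixed for every visit

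*Combined protocol and SAP*

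**What the plan says.** Protocol 7.6, under Questionnaires, gives the sequence: "After the incremental maximal ergometer exercise test, subjects will be asked to fill out four validated questionnaires to assess general health". The instruments follow: "This includes quality of life (SF-36v2), level of anxiety (GAD-7), level of depression (PHQ-9) and dietary pattern (Mediterranean Diet Score) of the patient". The next sentence gives a different mode: "These postal questionnaires will be completed at T0, T1 and T2".

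Earlier in 7.6 the text says "Patients will undergo several tests at one testing day", and the heading over these procedures opens "Testing day: Blood samples, Physical Fitness and Questionnaires (2 hours", so the questionnaires are counted as part of the visit.

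Protocol 7.5 states that "The patient, care provider and outcome assessor will not be blinded to the intervention itself because of safety concerns".

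The scores are secondary endpoints analysed as changes between visits (protocol 7.2.1). SAP section 9 analyses them with the model used for objective 1. SAP section 11 names three outcomes in particular for the cost-effectiveness ratios: change in peak VO2, the SF-36v2 Physical Component Summary (PCS) and the Mental Component Summary (MCS).

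**The concern.** Quality of life, depression and anxiety are self-reported by patients who know their arm. When they are answered after a maximal test, the answers can reflect how that test went. The plan expects the mCR arm to gain 3.0 ml/kg/min more than control on the test at 6 months (protocol 5.4). If the test experience or result reaches the patient first, the carry-over would run in the same direction as the treatment hypothesis.

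The conflict over mode is a separate matter. If some centres hand out the forms at the visit and others use the post, or a centre changes between T0 and T1, the change scores contain differences in setting and timing that have nothing to do with treatment.

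At stake are objective 5 and two of the three named cost-effectiveness denominators.

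**Working it through.** The plan gives no figure on this point, so the check is mainly a comparison of the text.

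**1. Two readings of protocol 7.6.**

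| Reading | What has to be wrong | What follows |
|---|---|---|
| Completed on the testing day | The word postal | Place and order are fixed, and the order is test first, questionnaires second |
| Completed by post | The order sentence, or at least its meaning, and the testing-day heading | Place and time are undefined; the forms may be completed before or after the test, on another day |

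The two problems are alternatives and should not be added together. Under either reading the paragraph needs correcting.

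**2. Safeguards looked for.**

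- Withholding the test result until the questionnaires are done: no such rule. Protocol 6.1 does use the T0 result in the mCR arm ("The outcomes of the maximal exercise tests on the first visit will enable to personalise the heart rate zones per patient"), but does not say when the patient learns it.
- An interval between test and questionnaires: none given.
- Constancy across visits: protocol 7.6 keeps the exercise-test modality the same at T0, T1 and T2. There is no matching rule for the questionnaires.
- Appendix I ticks the questionnaires at each visit and gives neither order nor mode.
- SAP section 9 refers to the model of section 5, which has no term or sensitivity analysis for order or mode.

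**3. What a between-arm bias would need.** The order is the same for both arms at every visit, so fatigue from the test is largely non-differential and mostly cancels in the between-arm comparison of changes. A bias also needs the test experience or result, or knowledge of the arm, to shift the answers differently by arm. The text permits this and does not show that it happens.

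**4. Scale, on an assumption that is not in the documents.** Suppose a fraction ρ of the expected standardised VO2peak difference carries over into a score that mCR does not otherwise affect.

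- Inputs (protocol 5.4): difference 3.0, SDs 5 and 6, two-sided 5% level, 119 per arm, 30% withdrawal.
- Pooled SD = √((25 + 36)/2) = 5.52. A t-based calculation on these inputs at 80% power gives 54.2, rounded up to 55 per group, the plan's own figure.
- Standardised difference = 3/5.52 = 0.54.
- Induced difference d = ρ × 0.54. Standard error = √(2/n), with n = 119 or n = 119 × 0.70 ≈ 83 per arm.
- Rejection rate = Φ(d/SE − 1.96) + Φ(−d/SE − 1.96), ignoring centre clustering.

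| ρ (assumed) | d in SD units | n = 83 per arm | n = 119 per arm |
|---|---|---|---|
| 0 | 0 | 5.0% | 5.0% |
| 0.1 | 0.054 | 6.4% | 7.0% |
| 0.2 | 0.109 | 10.8% | 13.4% |
| 0.3 | 0.163 | 18.3% | 24.2% |

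The table shows only how the error rate would respond to a given carry-over. Nothing in the documents supports any particular ρ, including a value above zero.

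**The case against.** The strongest reply is that the directional mechanism is not in the documents: no section says patients are told their VO2peak before they answer. Apart from the one word postal, the text points to the visit, so a site would probably use the testing day. The sequence is common to both arms. mCR patients also see their training data on a portal and receive coaching calls for six months (protocol 6.1 and 6.2), so they know their arm and their progress whatever the order on the day. Reordering removes at most an increment of an open-label problem that remains. Finally, protocol version 1.3 is dated July 2016 and the SAP July 2017. If patients are already enrolled, a change of order between a patient's T0 and T1 would itself disturb the change scores.

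Most of this stands. It rules out treating the bias as established, and it sets a condition on the remedy. Figure 2 of the protocol, on study procedures, was not available in the text checked and may show the visit sequence.

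Two things survive. The mode is stated in two incompatible ways, and nothing holds mode, timing or withholding of results constant for endpoints analysed as change scores. The likelier reading, on-site completion, is also the one with the less favourable order.

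**Conclusion.** The point holds as an inexpensive improvement to secondary outcomes. The text contradicts itself on mode, puts unblinded self-report after the maximal test, and has no rule that protects the answers from the test or keeps their conditions constant. Bias in SF-36v2, PHQ-9 and GAD-7, and so in the PCS and MCS cost-effectiveness ratios, is possible, but its size cannot be derived from the documents. The primary VO2peak endpoint is untouched.

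A reader might infer more than the documents support:

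- That results are fed back before the questionnaires and favour mCR. The documents only fail to prevent this.
- That exhaustion biases the comparison. It applies to both arms and mainly adds noise.
- That the diet score is affected in the same way. It falls under the same sentence, but no route from a fitness result to reported diet is apparent.
- That the rejection rates in the table estimate the error. They depend wholly on the assumed carry-over.

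**What to change.** Rewrite the Questionnaires paragraph of protocol 7.6 so that it:

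- states one mode, removing the conflict between postal completion and the testing day;
- has the four questionnaires completed before the exercise test and before any test result is given;
- applies the same mode and order at T0, T1 and T2 in both arms;
- requires the completion date to be recorded.

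Appendix I needs no change, because it gives no order within a visit.

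The cost is a few lines of wording and a different sequence inside the same 2-hour visit, with no added visit or procedure. The downside arises only if the change is made mid-trial. Patients already past T0 should then keep their T0 order and mode so that their change scores stay comparable, and order and mode should be recorded for everyone so that the two groups of patients can be told apart. The change does not remove the wider limitation of self-report in an open-label trial.

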**Information Collection MACE, Care Consumption**

The occurrence of events (MACE (21) [cardiovascular mortality, all-cause mortality, near sudden cardiac death, acute coronary syndrome, CV Intervention/surgery, CV hospital admission, CV emergency visits]) and utilisation of care ((days) admission, outpatient clinic visits, GP visits, interventions, cardiophysiology, radiology, nuclear and lab testing) will be collected by a monthly telephone call with the participants using a standardised schedule throughout the study period. The telephone calls will be performed by a nurse. No advices or support will be given to the participants regarding their daily exercise or lifestyle changes.

### **7.7 Withdrawal of individual subjects**

Patients can leave the study at any time for any reason if they wish to do so without any consequences. The site investigator can decide to withdraw a patient from the study for urgent medical reasons.

### **7.8 Replacement of individual subjects after withdrawal**

We will not replace patients after withdrawal of the study.

### **7.9 Follow-up of subjects withdrawn from treatment**

Patients in the study who experience a reintervention and get a new indication for CR will still be tested at 6 months and 12 months according to the original schedule. However, patients participating in the intervention group perceive no mobile telemonitoring guidance anymore. All patients will also be followed on major outcomes; relapse of myocardial infarction, death, PCI and CABG and utilisation of care.

### **7.10 Follow-up of subjects withdrawn from study**

Patients who leave the study prematurely without any reason or because of an experienced reintervention with a contraindication to CR as a consequence will be followed on major outcomes; relapse of heart infarct, death, PCI and CABG and utilisation of care.

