#### **9.5 Population**

The intention to treat population is used for analysis of the primary and secondary endpoints. All patients will be analysed in the group they are randomised to and whether or not they completed the *mCR* programme according to protocol.

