#### 4.7 Missing data

All collected data will be used in the data analysis, also data from the patient who discontinue the study until the time of study discontinuation. Missing data will be reported overall and by intervention and centre. We will describe patterns in missing data. We will analyse whether missing data are systematically different between both groups (*mCR* and control group) or whether they are related to baseline values or values on earlier time points. In case that the occurrence of missing values is systematically different between groups, or is related to other variables, multiple imputation methods will be used to calculate parameter estimates for sensitivity analysis.

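### After a reintervention with a contraindication to CR, Protocol 7.10 keeps only events and care use and makes no provision for the T1/T2 assessments that need no exercise

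*Combined protocol and SAP*

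**What the plan says.** Protocol 7.9 covers patients who have a reintervention and gain a new indication for CR. They "will still be tested at 6 months and 12 months according to the original schedule", although those in the intervention arm no longer receive telemonitoring guidance.

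Protocol 7.10 covers patients withdrawn from the study. It names those who leave without giving a reason and those who leave "because of an experienced reintervention with a contraindication to CR as a consequence". Both groups "will be followed on major outcomes; relapse of heart infarct, death, PCI and CABG and utilisation of care". It mentions no T1 or T2 assessment.

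Protocol 7.7 lets patients leave at will and adds: "The site investigator can decide to withdraw a patient from the study for urgent medical reasons".

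On measurement, Protocol 7.6 says of the SF-36v2, GAD-7, PHQ-9 and diet score: "These postal questionnaires will be completed at T0, T1 and T2". The same section plans blood samples and skinfolds, and Appendix I schedules laboratory tests, blood pressure and lean body mass at all three time points.

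On analysis, Protocol 9.5 sets intention to treat: "All patients will be analysed in the group they are randomised to and whether or not they completed the" mCR programme as planned. SAP 4.7 uses all collected data, "also data from the patient who discontinue the study until the time of study discontinuation". It plans multiple imputation only as a sensitivity analysis, and only if missingness proves to be related to group or to other variables. SAP 5.1 rules out imputation for the primary outcome.

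**The concern.** Suitability for CR concerns treatment. Whether a patient can return a questionnaire or give a blood sample is a separate matter. Under 7.9 and 7.10 the first decides the second: after a reintervention, T1/T2 testing is kept on one branch and not mentioned on the other.

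The event behind the split is not neutral. A reintervention falls under the cardiovascular intervention or surgery item of MACE. Patients whose reintervention also leaves them unsuitable for CR plausibly have poorer health than average. If they have no later values, the T1 and T2 results for objective 3 (risk factors) and objective 5 (general health) describe a population selected by a clinical outcome. The gap is avoidable, because these assessments are already scheduled for everyone and need no exercise.

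**Working it through.** **1. The two branches side by side**

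| Item at T1/T2 | 7.9: new CR indication | 7.10: left, contraindication to CR |
|---|---|---|
| Exercise test | kept | not mentioned |
| Questionnaires, laboratory tests, blood pressure, lean body mass | kept on the natural reading of testing on the original schedule | not mentioned |
| Infarct, death, PCI, CABG, care use | kept | kept |
| Near sudden cardiac death, ACS other than infarct | not named | not named |
| Cardiovascular admissions and emergency visits | through care use | only through care use |

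The care-use endpoint, much of the cost data and several MACE components therefore survive. The non-exercise outcomes of objectives 3 and 5 have no provision on the second branch.

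**2. What the analysis does with the gap**

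Objective 5 follows the SAP 5.1 approach, which models change adjusted for baseline. A patient with no T1 value has no T1 outcome in that model, and the reintervention is not a covariate. Objective 3 follows SAP 6, which adds a repeated-measures model. That model can use T1 if the patient left after T1, but again without the event. The conditional imputation would have few or no observed post-event values from this type of patient to draw on. It would lean on patients without the event and on 7.9 patients, who are those with a new CR indication.

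**3. Size of a possible shift**

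The documents give no rate for this event and no outcome difference, so every input here is an assumption. Let p be the fraction of an arm lost, and D the amount by which the lost patients would have scored worse than those who remain (beyond what baseline explains, on a scale where higher is better). With R the mean of those remaining:

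- Full-arm mean = (1 − p)R + p(R − D) = R − pD, so the observed mean is too high by pD.
- Bias in mCR minus control = p(mCR) × D(mCR) − p(control) × D(control).

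With D = 10 points in both arms:

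| Loss in mCR | Loss in control | Bias (points) |
|---|---|---|
| 3% (0.03 × 119 = 3.6 patients) | 0 | +0.3 |
| 8% (0.08 × 119 = 9.5 patients) | 0 | +0.8 |
| 5% | 5% | 0 |
| 0 | 8% | −0.8 |

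For VO2peak, assume 2% to 10% lost from one arm with a change 2 to 4 ml/kg/min worse. The shift is 0.02 × 2 = 0.04 to 0.10 × 4 = 0.40 ml/kg/min, or 1.3% to 13.3% of the planned 3.0.

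**4. Power is a lesser matter**

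The plan's sample size reproduces. The variances 25 and 36 give a root-mean-square SD of √(61/2) = 5.52. A difference of 3.0 at 80% power and two-sided 5% needs 54 per group by the normal formula and 55 by the noncentral t. A design effect of 1 + (11 − 1) × 0.05 = 1.5 (a cluster size of 11 reproduces this step) gives 82.5, so 83. Then 83/0.70 = 118.6, so 119.

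At 30% loss, 119 × 0.70 = 83.3 remain per arm. Dividing by 1.5 gives 55.5 effective patients and 81.7% power. If these losses fall within the 30%, nothing changes. If they come on top, power is 80.5% at 2% extra and 78.8% at 5% extra.

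**The case against.** Four stronger readings are tempting, and the text does not support them.

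- **That all T1/T2 outcomes are lost.** The same sentence of 7.10 keeps infarct, death, PCI, CABG and care use, and SAP 4.7 keeps everything collected before discontinuation.
- **That a contraindication forces the patient out.** Section 7.10 describes follow-up of those who leave for that reason and does not order removal. Withdrawal is governed by 7.7.
- **That the rule cannot apply to controls and so favours mCR.** Controls are in "the control group with no mobile telemonitoring guidance or other CR programme", but 7.10 speaks of patients in general, and a contraindication to CR is an entry exclusion in both arms (Protocol 5.3). It can be judged for anyone. Uneven use in an open trial is possible but is not stated. If mCR lowers event rates, as the fourth hypothesis expects, more controls would be lost and the bias would run against mCR.
- **That 7.10 contradicts intention to treat.** Protocol 9.5 and SAP 4.2.1 define who is analysed and in which group. They do not say which visits continue.

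Two further objections carry weight. A patient with a contraindication to CR may also be unable to do a maximal test. The documents do not say, so some VO2peak loss may be unavoidable. And although the questionnaires are called postal, 7.6 also places them after the exercise test on the testing day, with skinfolds just before it. A patient who does not attend could miss them unless the plan says otherwise.

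The planned missing-data checks are a partial answer only. They may detect the pattern, but they cannot supply the absent post-event values.

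**Conclusion.** The point holds in limited form. Read as written, 7.10 keeps events and care use but provides for no T1/T2 questionnaires, laboratory tests, blood pressure or body measurements after a reintervention with a contraindication to CR, while 7.9 keeps testing after a reintervention with a new indication. Missingness for objectives 3 and 5 then depends on an event that is part of MACE, and the planned analysis offers only a conditional sensitivity analysis.

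The documents allow neither the size nor the direction of the bias to be stated. The range of 0.3 to 0.8 points rests wholly on an assumed 3% to 8% loss, an assumed 10-point gap and loss from one arm only. With equal loss and equal gaps it is about zero. The effect on the primary endpoint is uncertain, and the effect on power is small within the 30% allowance. This is a cheap improvement to the plan and does not invalidate the trial.

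**What to change.** Reconcile Protocol 7.7, 7.9 and 7.10 with SAP 4.7, so that stopping the intervention is distinguished from leaving the study. Then state three things:

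1. The already scheduled T1/T2 assessments that need no exercise (SF-36v2, PHQ-9, GAD-7, diet score, laboratory tests, blood pressure, lean body mass) continue in both arms for patients who agree, and can be completed without the exercise test.
2. Collection of adverse events, all MACE components and care use continues likewise.
3. These data enter the intention-to-treat analysis. SAP 4.7 should no longer leave room to read the discontinuation date as a cut-off for data that 7.10 goes on collecting.

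Treatment stopping and eligibility for the exercise test are left to the sponsor and centres, and no clinical rule is proposed here. The cost is protocol and SAP wording, plus assessments already in the schedule. The downside is a small added burden on a few ill patients, who may decline.
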